Estimated/ adjusted mean differences and Cohen's d's are reported for continuous outcomes. Cohen's d's with standard deviation at baseline in the denominator are reported for the treatment effects from results of linear mixed effects models. Estimated/ adjusted odds ratios are reported for dichotomous outcomes together with absolute values. Confidence intervals are reported at the 95% level, two-sided.

Tertiary trial objectives to investigate any influences of baseline risk factors and predictors on iCT-R intervention effects on outcomes, such as PTSD or MDD diagnoses, psychological distress, or well-being, are tested using linear and logistic mixed effects models using the same analysis principles as for the primary and secondary trial objectives. The main effects of the respective baseline risk factors and predictors (time-invariant covariates) and the two-way interactions between each of those baseline predictors and time (categorical: post-intervention, 1-year follow-up; level 1) are analysed. Baseline scores of PTSD or MDD symptom severity, or psychological distress, or well-being are used as covariates.

In case of any significant interaction effects between time and baseline moderators, simple slope analyses are carried out to investigate the direction of any moderation effects. Further tertiary trial objectives to investigate whether changes in process measures, such as rumination, intrusive memories, and concrete thinking, from baseline to post-intervention in the iCT-R condition predict PTSD and MDD diagnoses at 1-year follow-up will be analysed using logistic regressions with difference scores from pre to post for the process measures and baseline scores of PTSD or MDD symptom severity as covariate.

CACE and sensitivity analyses are conducted for the primary trial objectives.

Results are reported in APA format.

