#### **Description of Compliance with Intervention**

Level of compliance will be defined as 1) number of online modules completed during the intervention, 2) practice of tools.

A complier-average causal effect analysis (CACE) is used to test any influence of compliance on the intent-to-treat intervention effect of the primary trial objective analyses.

1067

1068

1069 **Reliability**

1070           The primary outcome measures, such as Structured Interviews by clinicians and self-  
1071 reports for the primary outcomes and nearly all of the secondary outcome measures are  
1072 standard instruments that have been validated and have shown good reliability.

1073           Scoring is done as described in the manuals or publications for the measures and  
1074 relevant sub-scales and Cronbach's Alphas are reported for the study sample.

1075           Interrater-reliability is reported for 1-year follow-up data. 10% of diagnoses at 1-year  
1076 follow-up are rated by a second rater.

1077           To ensure consistency in the data, validation checks on the data are carried out before  
1078 locking the dataset and analysis of the data. These include checking for potential data entry  
1079 mistakes, duplicate records, checking the range of variable values, missing data value codes,  
1080 etc.

1081 **ANALYSIS**

1082 **Outcome Definitions**

1083 Outcome measures:

1084           The primary outcome measure for the primary trial objective is PTSD and MDD  
1085 diagnoses (SCID-5;). Secondary outcomes with regards to the primary trial objective are  
1086 PTSD symptom severity (PCL-5) and MDD symptom severity (PHQ-9).

1087

1088           Outcome measures for the secondary trial objectives include resilience measures  
1089 (Wagnild-Resilience Scale and CD-RISC, both continuous), well-being measures (subscale  
1090 rumination of the RIQ, GAD-7, GHQ-12, WEMWBS), general health measures (weight and  
1091 height; Insomnia severity index; Smoking Behaviour Questionnaire, sum score for both  
1092 items; Alcohol Use Questionnaire, unit increase/ decrease/ stayed the same), health economic  
1093 costs (intervention costs per QALY gained based on 4 measures), and hormone and immune  
1094 function (collected with saliva samples and CRP plasma).

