In case of a significant main effect of intervention group or interaction effect between intervention group and time with regards to the primary outcome measure (PTSD and MDD diagnoses) and secondary outcome measures for the primary trial objective (PTSD and MDD symptom severity), intervention group comparisons are carried out using pairwise contrasts. iCT-R (coded as '1') is tested against Mind-Online (coded as '0') and a significant main effect or interaction in favour of iCT-R indicates intervention superiority (comparison of highest priority) of the newly developed resilience intervention over the existing online intervention. In a second step, iCT-R (coded as '1') is then tested against Standard Practice

(coded as '0') and again, a significant main effect or interaction in favour of iCT-R indicates intervention superiority for the newly developed intervention over usual Standard Practice. In a third step, Mind-Online (coded as '1') is tested against Standard Practice (coded as '0') and a significant main effect or interaction in favour of Mind-Online indicates intervention superiority of the existing online intervention compared to Standard Practice.

Adjusted/ estimated mean differences and Cohen's d's with standard deviation at baseline in the denominator are reported in tables for continuous outcomes for the intervention effects from results of linear mixed effects models and frequencies of diagnoses (absolute numbers and percentages) and absolute values as well as estimated/ adjusted odds ratios are reported for dichotomous outcomes.

All significance tests are carried out on a  $p < .05$  level, two-sided, and confidence intervals are reported on the 95% level.

Analyses of secondary trial objectives:

Any intervention effects on the secondary outcome measures, such as resilience (Connor-Davidson Resilience Scale,; Wagnild Resilience Scale), rumination (ruminative responses brooding subscale; Responses to Intrusions Questionnaire rumination subscale), anxiety (GAD-7), Smoking Behaviour (Smoking Behaviour Questionnaire), Alcohol consumption (Alcohol Use Questionnaire), psychological distress (GHQ), well-being (Warwick Edinburgh Mental Wellbeing Scale), sleep quality (Insomnia severity index), and weight, are analysed for the short-term primary outcome time point of 1-year and for the long-term primary outcome time point of 2-years follow-up, once completed.

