Linear mixed effects models are specified for these continuous outcome measures. Intervention condition (categorical; iCT-R versus Mind-Online versus Standard Practice; level 2) and the interaction between intervention time (categorical; post-intervention, 1-year-follow-up, 2-years-follow-up once completed; level 1) are specified as fixed effects predictors in the models.

Baseline values for the respective secondary outcome are added as covariate in these models together with PTSD and MDD symptom severity at baseline, and randomisation factors.

Adjusted/ estimated mean differences and Cohen's d's with standard deviation at baseline in the denominator are reported in tables for continuous outcomes for the intervention effects from results of linear mixed effects models.

The health economic analyses will be conducted and reported by [name] and and hormone and immune function are tested by collaborators and are therefore not part of this statistical analysis plan. A plan for the health economic and hormone and immune function analyses will be agreed.

Analyses of the tertiary trial objectives:

In order to investigate whether risk factors and predictors at baseline, such as level of social support, trauma exposure, demographic data, past and current comorbidities, neuroticism as a personality factor, level of concrete thinking, and frequency/ duration/ distress with regards to intrusive memories, influence any iCT-R intervention effects on PTSD or MDD diagnoses, psychological distress, and well-being at 1-year follow-up, a mixed effects model for each of the outcomes, PTSD and MDD diagnoses, psychological distress, and well-being, is specified with baseline scores of PTSD or MDD symptom severity or psychological distress or well-being as covariate. The main effects of the respective baseline predictors (time-invariant covariates) and the two-way interactions between each of those baseline predictors and time (categorical: post-intervention, 1-year follow-up; level 1) will be analysed.

Again, Maximum Likelihood is used if the assumption of normality of the residuals of the outcomes is fulfilled. An unstructured variance-covariance structure matrix is used, all significance tests are carried out on a  $p < .05$  level, two-sided, and confidence intervals are reported at the 95% level.

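### The alcohol outcome reads as a three-level change item, but the SAP analyses it as continuous, without stating codes and with an effect size that may be undefined

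*Combined protocol and SAP*

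**What the plan says.** The SAP's Outcome Definitions list the measures for the secondary objectives. The two resilience instruments are marked explicitly ("Wagnild-Resilience Scale and CD-RISC, both continuous") and smoking is given a sum score. Alcohol is described as "Alcohol Use Questionnaire, unit increase/ decrease/ stayed the same".

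Analysis Methods, under the secondary trial objectives, names alcohol consumption beside the anxiety, distress, wellbeing and insomnia scales. It then covers the whole list in one sentence: "Linear mixed effects models are specified for these continuous outcome measures". No exception is made for alcohol. On adjustment it says "Baseline values for the respective secondary outcome are added as covariate in these models", together with baseline PTSD and MDD severity and the randomisation factors. On reporting it says "Cohen's d's with standard deviation at baseline in the denominator are reported in tables for continuous outcomes".

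The only provision for non-continuous outcomes is in the Statistical Analysis Outline: "Estimated/ adjusted odds ratios are reported for dichotomous outcomes together with absolute values". No ordinal or multinomial model appears in the protocol or SAP. The fallback for failed model assumptions is resampling.

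The protocol calls the smoking and alcohol questionnaire unpublished and does not reproduce its items. Its schedule of procedures (Appendix B) places the questionnaire at baseline and at 6, 52 and 104 weeks.

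**The concern.** An answer of up, down or unchanged is an ordered category about change. A linear mixed model needs numbers, and the SAP does not say which numbers the three answers receive. The model also needs a baseline value of the same quantity, and d needs that quantity's baseline SD. A change item may have neither, and the SAP does not state the period to which the change refers.

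Alcohol use is a named secondary outcome in both protocol and SAP. As written, the analyst must choose the codes, the reference period and the divisor for d when the data are already in hand. Those choices can move the size of the reported effect and even its sign.

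**Working it through.** **1. The plan's own sample size.** Inputs from protocol 11.2 and the SAP's Sample Size section: risks 25% and 12.5%, power 80%, two-sided alpha 0.05.

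- Odds ratio: (0.125/0.875)/(0.25/0.75) = 0.429.
- n per arm = [1.96 × √(2 × 0.1875 × 0.8125) + 0.8416 × √(0.1875 + 0.1094)]² / 0.125² = (1.0819 + 0.4586)² / 0.015625 = 151.9, so 152.
- Total: 3 × 152 = 456, and 456/0.80 = 570.

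The plan's figures reproduce. The alcohol point does not depend on them; 152 per arm is used below only as the analysable arm size.

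**2. Codes.** Assumed shares for illustration: arm A 20% decrease, 50% same, 30% increase; arm B 30%, 50%, 20%.

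- Ordered codes (decrease 1, same 2, increase 3): A = 0.2 + 1.0 + 0.9 = 2.1; B = 0.3 + 1.0 + 0.6 = 1.9; B - A = -0.20.
- Codes in the order the SAP lists the answers (increase 1, decrease 2, same 3): A = 0.3 + 0.4 + 1.5 = 2.2; B = 0.2 + 0.6 + 1.5 = 2.3; B - A = +0.10.

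The same data give opposite signs, and nothing in the SAP selects between the two codings.

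**3. Baseline covariate and d.**

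- If change is counted from trial baseline, everyone is unchanged at baseline. The covariate is constant, its SD is 0, and d = -0.20/0 is undefined.
- If the baseline answer refers to an earlier period, a covariate and an SD exist, but they describe a different change. For the same difference of -0.20, d is -0.20/0.3 = -0.67 with a baseline SD of 0.3 and -0.20/0.9 = -0.22 with 0.9 (both SDs assumed).

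**4. Cost of collapsing units to three levels.** Assumptions: change in units is normal with SD 1 and mean 0 in the comparator; the shift is 0.3225 SD, chosen to give about 80% power on raw units; 152 per arm; answers coded -1/0/+1, with changes within ±b counted as unchanged.

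- Raw units: 0.3225 × √(152/2) = 2.81; Φ(2.81 - 1.96) = 0.80.
- b = 0.1: comparator 46.0% down, 46.0% up (variance 0.920); shifted arm 58.8% down, 33.6% up (mean -0.252, variance 0.861). SE = √((0.920 + 0.861)/152) = 0.108; z = 2.33; power 0.64.
- b = 0.6: comparator 27.4% down, 27.4% up (variance 0.549); shifted arm 39.1% down, 17.8% up (mean -0.213, variance 0.524). SE = 0.084; z = 2.53; power 0.716, or 0.71 by simulation.

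**5. What an ordinal model changes.**

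- In the step 2 example the odds ratio for B against A being in a lower category is (0.3/0.7)/(0.2/0.8) = 1.71 at the first cut and (0.8/0.2)/(0.7/0.3) = 1.71 at the second. This is one interpretable effect with no need for spacing or a baseline SD.
- Power is unchanged. On the three-level data, simulated power for the t test and the rank test was 0.64 and 0.63 at b = 0.1, and 0.71 for both at b = 0.6.

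**The case against.** The strongest reply is that the instrument is not visible. The questionnaire is unpublished, and the SAP refers the reader to the published protocol paper for details of the measures. The word unit may mean alcohol units, with the rest a loose description of numeric change. A linear model would then be reasonable. This stands, and it limits confidence. It does not remove the point: the phrase reads more naturally as three answers, and a numeric change from trial baseline would still have no usable baseline value or SD.

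A reader might infer more than the documents support in four ways:

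- **That a mean of the three answers has no meaning.** Scored -1/0/+1, it is the share increasing minus the share decreasing. The defect is that no such scores are stated.
- **That no baseline value exists.** The questionnaire is scheduled at baseline. The value is absent or constant only if the item measures change from trial baseline, which the SAP does not say.
- **That the linear model causes the power loss.** The loss comes from collapsing units; a rank test on the same three levels loses as much.
- **That a linear model hides differences an ordinal one would find.** Shares of 15/70/15% and 40/20/40% both have mean 0 on -1/0/+1 codes. A proportional-odds model misses this too: the two cumulative odds ratios are (0.40/0.60)/(0.15/0.85) = 3.78 and (0.60/0.40)/(0.85/0.15) = 0.26. Their logs cancel, so the fitted common log odds ratio is 0 (p = 1).

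The resampling fallback is a fair answer to non-normal residuals. It does not supply codes, a reference period or a divisor for d.

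**Conclusion.** The mismatch is in the current SAP text and nothing elsewhere resolves it. For a three-level change item, the stated rule leaves the sign of the mean difference open to the coding, and gives a Cohen's d that is either undefined or scaled by an arbitrary SD.

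The power range of 64-71% rests on the normal-change and band assumptions in the working. It argues only for analysing units where they are recorded, not for an ordinal model over a linear one. The case for the ordinal model is interpretability alone.

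The scope is one secondary outcome. Confidence is medium, because the item wording and its reference period are not shown. The change is cheap and worth making before the alcohol data are analysed.

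**What to change.** State in Outcome Definitions what the alcohol item asks, over what period, and how it is scored. Then take one of two routes.

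- **Units recorded at each visit:** define the outcome as units at follow-up and keep the linear mixed model, adjusted for baseline units. The baseline-SD d is then defined.
- **Only the three-level item:** use an ordinal (proportional-odds) mixed model for decrease, same, increase, with arm, time, arm-by-time, baseline PTSD and MDD severity and the randomisation factors. Report a common odds ratio and the category percentages by arm; the percentages would also show a symmetric spread that the odds ratio cannot. Drop the baseline-SD d, and drop any baseline-value covariate that does not exist on the same scale.

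The cost is one paragraph of SAP text and, on the second route, one extra model. The downside of that route is an odds ratio in place of d for this outcome, so it cannot be tabulated on the same scale as the other secondary outcomes.

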| Tertiary Objectives

1. Do psychiatric, personality, trauma and social support factors at baseline (social support, trauma exposure, anxiety, age, gender, education, neuroticism, past and current psychiatric status, immune function) influence (i.e., moderate) levels of symptoms (PTSD or MD) psychological distress and wellbeing at follow-up?

2. Do changes in resilience-related factors (rumination, responses to intrusions, concrete thinking, resilience appraisals, practice of iCT-R/Mind-Online tools) mediate symptom levels of PTSD and MD at one year follow-up with iCT-R and Mind-Online?

3. Do changes in resilience-related factors (rumination, responses to intrusions, concrete thinking, resilience appraisals, practice of iCT-R/Mind-Online tools) mediate symptom levels of PTSD and MD at two year follow-up with iCT-R and Mind-Online?

4. Does concrete thinking, practice of tools and responses to intrusions at 6 months predict diagnoses and levels of PTSD and depression symptoms at one year? | 1.
Neuroticism: Eysenck Personality Questionnaire, Neuroticism subscale (EPQ) 
Social Support (SS) adapted from 36
Age, gender, education: Demographic Questionnaire (unpublished)
Psychological Distress: GHQ 
Wellbeing: WEMWBS 
Immune function: CRP
Hormone function: Cortisol

1., 2., 3 and 4
Past & Current Psychiatric Status: Structured Clinical Interview for DSM-V 
Symptoms PTSD: PCL-5 
Symptoms Depression: PHQ-9 
Anxiety: GAD-7 
Trauma Exposure: Trauma Screener (unpublished)

2. and 3.
Rumination: Ruminative Response Scale  (Brooding Subscale)
Intrusions: Response to Intrusions Questionnaire (RIQ)  , short version
Duration, Frequency, Distress Linked to Intrusions (unpublished)
Concrete Thinking: Concrete & Abstract Thinking (unpublished)
Practice iCT-R/Mind Online tools (unpublished)
Resilience: CD-RISC  & Resilience | 1.
Baseline
6 weeks
52 weeks
104 weeks

2. and 3.
Baseline
6 weeks
52 weeks
104 weeks

4.
Baseline
6 weeks
24 weeks |

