## **Objectives**

The primary trial objective is to evaluate whether the newly developed iCT-R intervention is more effective than the existing Mind-Online intervention at 1-year and at 2-years follow-up with regards to PTSD and MDD diagnoses.

Secondary trial objectives are to evaluate the efficacy of iCT-R compared to Mind-Online at 1-year and at 2-year follow-up with regards to secondary outcomes, such as resilience and well-being measures, as well as general health measures, and in terms of health economic costs. Furthermore, the effects of iCT-R versus Mind-Online on immune and hormone function will be compared at post-intervention.

Tertiary trial objectives are to investigate whether risk factors and predictors at baseline, such as level of social support, trauma exposure, demographic data, neuroticism as a personality factor, level of concrete thinking, frequency, duration, and distress with regards to intrusive memories influence any effects of iCT-R on PTSD and MDD diagnoses, psychological distress, and well-being at 1-year follow-up.

Further tertiary objectives are to investigate whether changes from baseline to post-intervention in resilience factors, such as rumination, responses to intrusive memories, level of concrete thinking, and resilience appraisals, predict PTSD and MDD diagnoses at 1-year follow-up in the iCT-R intervention group.

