In case of any significant interaction effects between time and baseline moderators, simple slope analyses are carried out to investigate the direction of any moderation effects.

Further tertiary trial objectives to investigate whether changes (decrease) in process measures, such as rumination, intrusive memories, and increases in concrete thinking, from baseline to post-intervention in the iCT-R condition predict lack of PTSD or MDD diagnoses

[name], [name], [name], [name], [name], [name], [name], [name], [name], [name], [name], & [name] Cognitive resilience training to prevent PTSD and MDD in paramedics: A randomised controlled trial.

(versus presence of PTSD or MDD diagnoses) at 1-year follow-up are analysed using logistic regressions with difference scores from pre to post for the process measures and baseline scores of PTSD or MDD symptom severity as covariate.

CACE analysis:

A complier-average causal effect analysis (CACE) is used to test the influence of compliance on the intent-to-treat intervention effect of the primary trial objectives/ analyses. Magnitude of compliance will be defined as 1) number of online modules completed during the intervention, and 2) practice of tools. Based on these variables, trajectories of compliance are determined. CACE will then be compared with the intent-to-treat intervention effects resulting from the primary analyses and the results will be reported.

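### The SAP's moderator model has no baseline-factor-by-arm term, so it tests prognosis for change, not moderation of the iCT-R effect; the protocol's mediation objectives are also left unreconciled

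*Combined protocol and SAP*

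**What the plan says.** **Moderation.** SAP 2.2 (Objectives) asks whether baseline factors "influence any effects of iCT-R on PTSD and MDD diagnoses, psychological distress, and well-being at 1-year follow-up", and SAP 6.2 (Analysis Methods) repeats the aim. For the model, SAP 3.7 (Statistical Analysis Outline) gives the factors' main effects and "the two-way interactions between each of those baseline predictors and time (categorical: post-intervention, 1-year follow-up; level 1) are analysed". SAP 6.2 says the same: besides the main effects, "the two-way interactions between each of those baseline predictors and time (categorical: post-intervention, 1-year follow-up; level 1) will be analysed". The next step is: "In case of any significant interaction effects between time and baseline moderators, simple slope analyses are carried out to investigate the direction" of any moderation. SAP 3.7 also says that the tertiary models follow the principles of the primary and secondary ones.

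The protocol's tertiary objective 1 (section 5) is looser. It asks whether baseline factors "influence (i.e., moderate) levels of symptoms (PTSD or MD) psychological distress and wellbeing at follow-up".

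**Process measures.** Protocol tertiary objective 2 asks whether changes in resilience-related factors "mediate symptom levels of PTSD and MD at one year follow-up with iCT-R and Mind-Online". Objective 3 asks the same at two years, and protocol 11.1 plans a process evaluation of moderators and mediators. SAP 2.2 restates the aim as prediction of 1-year diagnoses within the iCT-R group. SAP 3.7 plans that changes "from baseline to post-intervention in the iCT-R condition predict PTSD and MDD diagnoses at 1-year follow-up will be analysed using logistic regressions", using pre-to-post difference scores and baseline severity.

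**The concern.** Moderation of an intervention effect is a difference between arms that varies with a baseline factor. A model with no product of factor and arm cannot estimate it. Followed literally, the SAP's rule could report a factor that predicts worsening in every arm as a moderator of iCT-R, and could pass over a factor that changes the benefit equally at both visits. Such findings might later guide who is offered the training.

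The second issue is one of traceability. The protocol poses a two-arm mediation question about symptom levels at two time points. The SAP contains a one-arm prediction of diagnosis at one time point and gives no reason for the change. A reader who goes from the protocol's objectives to the SAP's results could take one for the other.

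**Working it through.** **1. The plan's own figure.** Protocol 11.2 uses 25% (full plus subsyndromal) against 12.5%, two-sided 5%, 80% power. With mean rate 0.1875:

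n = [1.960·√(2×0.1875×0.8125) + 0.842·√(0.25×0.75 + 0.125×0.875)]² / 0.125² = (1.0819 + 0.4586)² / 0.015625 = 151.9, so 152 per arm and 304 for two arms. Then 3 × 152 = 456, and 456 / 0.8 = 570. The stated figures reproduce. No figure is given for the tertiary analyses, so 152 per arm is used below.

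**2. Terms needed against terms named.**
- Needed: factor × arm and factor × arm × time, read at 1 year.
- Named in SAP 3.7 and 6.2: factor, and factor × time.
- Possibly inherited from the primary model: arm, and arm × time.
- Named in SAP 6.6 for Covid status: covariate × arm, and covariate × time × arm.

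**3. What factor × time estimates.** Let the slope of the outcome on the factor, in arm a at visit t, be β + γ(t) + δ(a) + η(a,t).
- Moderation at 1 year, iCT-R (I) against Mind-Online (M): [δ(I) + η(I,1yr)] − [δ(M) + η(M,1yr)].
- Factor × time without arm products: [γ(1yr) − γ(post)] plus the average over arms of [η(a,1yr) − η(a,post)].

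If moderation is constant over time, all η are zero. Then δ drops out of the second line, and the test rejects only at its nominal level (exactly so in the linear models; the logistic models behave in essentially the same way on the log-odds scale). If the factor is only prognostic for change, γ alone drives the test. If moderation grows in iCT-R only, it enters diluted to one third under 1:1:1 allocation and cannot be attributed to an arm.

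**4. Illustration with assumed effects.** Three arms of 152, a 50:50 binary factor, two visits with correlation 0.5, total SD about 1, continuous outcome, 2,000 runs; factor × arm was tested on the mean of the two visits.

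| Assumed truth | factor × time rejects | factor × arm rejects |
|---|---|---|
| Moderation of 0.7 in iCT-R at both visits | 5.4% | 94% |
| Prognostic only: 0.35 at 1 year in every arm | 96% | 5% |

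The percentages move with the assumed effects. The pattern does not, because it follows from step 3.

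**5. Power of the appropriate test.** For a standardised factor, unit residual SD and one visit, the SE of the difference in slopes is √(2/152) = 0.115, and power is about Φ(effect/0.115 − 1.96). This gives 80% at 0.32 SD, 41% at 0.20 and 14% at 0.10.

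For diagnoses, assume a 50:50 factor (76 per cell), 25% in both arms of one stratum, and 25% against 12.5% in the other:
- Difference in log odds ratios = ln(0.429) = −0.847.
- SE = √[3/(76×0.1875) + 1/(76×0.1094)] = 0.575.
- Power about 31%.

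If the responsive stratum falls to 6.25%, the difference is −1.609, the SE 0.660 and the power about 68%.

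**6. Events for the within-iCT-R regression.** SAP 3.5 gives pooled 1-year rates of 8.7% (PTSD) and 15.8% (depression).
- Equal arms: 152 × 0.087 = 13.2; 152 × 0.158 = 24.0.
- iCT-R at half the rate of both other arms: pooled = (1 + 1 + 0.5)/3 = 0.833 of the control rate, so the iCT-R rate is 0.5/0.833 = 0.6 of pooled. Events: 152 × 0.0522 = 7.9; 152 × 0.0948 = 14.4.

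**7. Prediction is not mediation.** In 1,000 simulated trials with no intervention effect on process change or outcome, the iCT-R-only regression found change predictive in 81%. The arm-to-process path rejected in 4% and the total effect in 6%. The assumed strength (0.6 log odds per SD of change) and event rate (about 20% at average covariate values, above the pooled single-diagnosis rates) come from no document, so 81% is not a forecast for this trial.

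**The case against.** - **Arm is in the model.** The reference to the primary models' principles probably brings in arm and arm × time, so it would be wrong to say that the SAP fits factor terms alone. This stands. It does not supply factor × arm.
- **Objective 1 may mean prognosis.** The protocol's wording can be read that way, and the planned terms partly answer that question. This stands for the protocol. The SAP's objective speaks of effects of iCT-R and cannot be read so.
- **Subgroups are covered.** SAP 6.5 shows iCT-R effects by higher or lower baseline severity in forest plots. This covers one factor and states no interaction test.
- **The process regression answers its own question.** A reader might infer that this model, too, cannot meet its objective. The documents do not support that: SAP 2.2 asks about prediction within iCT-R, the regression addresses that, and the SAP never calls it mediation or claims a mechanism. What remains is the unexplained difference from protocol objectives 2 and 3.
- **Mediation modelling has its own weakness.** The mediator is not randomised, so an indirect-effect model rests on no unmeasured mediator-outcome confounding. This stands and must be stated with any such model.
- **Sparse events.** The SAP speaks of regressions in the plural and does not say whether the change scores enter jointly, so overfitting cannot be asserted.

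**Conclusion.** The moderation analysis is wrong as written for the SAP's stated objective. The omission appears in both SAP 3.7 and 6.2, while SAP 6.6 uses the right form for Covid status, so it does not look like a single slip. The direction of the error rests only on the model terms; the simulated percentages rest on assumed effects.

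It does not follow that every true moderator will be missed, since moderation that changes over time can partly show in factor × time. Nor would the appropriate test be strong: for diagnoses its power is about 31% to 68% under the assumptions shown.

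The process analysis is a protocol-SAP mismatch. The comparator, the arm-to-process path, the indirect effect, the symptom outcome and the two-year analysis are absent from the SAP, and its version table, being for a first issue, records no change. About 13 PTSD and 24 depression events are expected in 152 iCT-R participants if arms are equal, and about 8 and 14 if iCT-R halves the risk. Both points concern tertiary objectives. The primary analysis and the sample size are untouched.

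**What to change.** **Moderation.** In SAP 3.7 and 6.2, specify factor, arm, time, factor × time, arm × time, factor × arm and factor × arm × time. Define the moderation test as the factor × (iCT-R versus Mind-Online) contrast at 1 year. Let simple-effect analyses follow only that contrast. State that all arms are included, and label the results exploratory. Factor × time may be kept, reported as prognosis.

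**Process measures.** Choose one and record the reason:
1. Keep the regression, call it within-arm prediction, and state that it does not address protocol objectives 2 and 3.
2. Add an exploratory iCT-R versus Mind-Online model for PCL-5 and PHQ-9 at 1 and 2 years: arm to process change from baseline to 6 weeks; then outcome on arm, process change, baseline process score and baseline severity. Report the indirect effect with a bootstrap confidence interval, and state that the mediator is not randomised and that no unmeasured mediator-outcome confounding is assumed.

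Either way, say whether the change scores enter one model or separate ones, and report the event counts.

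**Cost.** SAP wording and extra model terms. The measures needed are already in the protocol's Appendix B schedule. The price is wider intervals and lower power than the factor × time test appears to offer, and the extra terms may be hard to fit for diagnoses with few events.
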